### Sample size calculation

According to the data from the participating centers in the past 2 years and the data presented from the range of previous studies [27–29], the incidence of early BPD in infants with gestational age 26^+0^ to 30^+6^ weeks was 68–77%, and 40% developed moderate or severe BPD. The effect of HC therapy was assumed to reduce moderate or severe BPD (the primary endpoint) to 25% or less (number needed to treat, NNT = 5). Adopting a maximum significance level of *α* = 0.05 and a minimum test power of 80%, the number of subjects per group will be *N* = 81, which will be increased by 20% to compensate for potential dropouts during the follow-up, leading to 98 subjects per group (total 98 × 2 = 196 subjects).

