#### Long-term outcomes after hospital discharge

Neurodevelopmental impairment at 104 weeks corrected age: The Bayley Scales of Infant and Toddler Development, Second Edition (BSID II) will be used in this trial.
Cognitive delay: defined as a cognitive score less than 80.Language delay: defined as a language score less than 80.Cerebral palsy and severity of cerebral palsy using the gross motor function classification system.Hearing loss requiring hearing aids at 104 weeks corrected age.Blindness at 104 weeks corrected age: vision loss with only form or shadow vision or no useful vision.Number of readmissions in the first year since the first discharge home.Weight, length, and head circumference at 40 weeks postmenstrual age and 12, 26, 52, and 104 weeks corrected age.Premature birth-related mortality from enrollment to 104 weeks corrected age.Behavioral problems (child behavior checklist) at 104 weeks corrected age. The scores on the checklist will be compared between groups.

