### Clinical data collection

At the time of randomization, baseline data will be collected from all included patients, including maternal and patient characteristics. Demographic data will include sex, birth weight, gestational age, 5-min Apgar score, surfactant therapy, prenatal corticosteroid use, premature rupture of the membrane before the onset of labor (> 18 h), singleton/multiple birth, and mode of delivery. Population characteristics will be used to compare outcomes between the two groups.

The following clinical data will be collected: continuous positive airway pressure (CPAP)-assisted time, invasive ventilator-assisted time, days of hospitalization, days on supplemental oxygen, IVH, spontaneous intestinal perforation, NEC, and ROP.

During HC treatment, respiratory support, blood sugar, blood pressure, and anthropometric data will be collected. Outcome variables and cointerventions will be recorded at 36 weeks PMA.

After discharge, one trained investigator in each center will follow up all patients at 40 weeks PMA and at 12, 26, 52, and 104 weeks corrected age. We will provide free neurodevelopmental impairment examinations to promote follow-up rates. For potential dropouts during the follow-up, we will expand the sample size by 20% and the missing data will be ignored in the analysis. The outcomes at each time point mentioned above will be collected by the investigators (Table 1).

**Table 1 Tab1:** SPIRIT figure: showing time points for enrollment, interventions, and assessment

	Study period						
	Enrollment	Allocation	Post-allocation				Close-out
Time point	At 4 weeks after birth	At 4 weeks after birth	At 36 weeks postmenstrual age	At 40 weeks postmenstrual age	At 12, 26 weeks corrected age	At 52 weeks corrected age	At 104 weeks corrected age
Enrollment:							
Eligibility screen	X						
Informed consent	X						
Demographic data	X						
Allocation		X					
Intervention:							
Hydrocortisone		X					
Placebo		X					
Assessments:							
Baseline variables assessments	X	X					
Primary outcome			X				
Secondary outcomes:							
Brain volume				X			
Others			X				
Long-term outcomes:							
Neurodevelopmental impairment, hearing loss, and blindness							X
Number of readmissions						X	
Weight, length, and head circumference				X	X	X	X
Behavioral problems, premature birth-related mortality							X

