### Statistical analysis

The analyses will be based on the intention-to-treat (ITT) principle in accordance with the Consolidated Standards of Reporting Trials (CONSORT). Statistical analyses will be performed with SAS version 9.2 (SAS Institute, Cary, North Carolina). Data will be presented as the mean ± standard deviation or median and interquartile range depending on their distribution. Categorical data, including the primary outcome, will be analyzed using the chi-square test between two groups. Continuous data will be analyzed using Student’s *t* test or the Mann-Whitney test as appropriate. The effect of HC on the dichotomous outcomes will be assessed by multivariable logistic regression analysis including possible confounders, including birth weight and gestational age. Statistical results will be reported as point estimates and 95% confidence intervals.

Mid-term data analysis will be conducted after inclusion of the first 98 patients. The principal investigator will decide whether any measure should be taken in light of the results. Case report forms (CRFs) will be entered by two independent researchers to ensure accuracy.

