### Ethical and academic management

The research protocol was reviewed and approved by the Ethics Committee of Southwest Medical University, and we will not begin recruiting at other centers in the trial until local ethical approval has been obtained. The ethics committee will be responsible for supervising all procedures of the study. Prior to making any changes to the study protocol, a written application will be submitted to the ethics committee for approval, and new written informed consent will be obtained from the guardians.

An independent academic board, which is composed of competent department, data monitoring, and safety management advisors, has been implemented to oversee unwanted effects and risks, as well as the collection and management of the data. The academic board will review all research data every 3 months. Until the included patients are discharged, each potential adverse effect will be monitored and reported to the academic board within 48 h. All members of the academic board are independent of the sponsor and trial investigators and free of competing interests.

Participants, as well as the researchers, evaluators, doctors, and nurses who are responsible for screening, recruitment, dispensing medicine, and outcome assessment, will remain blinded to treatment allocations. The researchers conducting the statistical analysis will know only the group codes but not the corresponding interventions. When severe adverse effects occur, the academic board has the right to unseal emergency envelopes. The reason for unblinding and time will be recorded. We prepared an insurance policy for every participant. This will provide ancillary and posttrial care in the case of any harm resulting from participation in the clinical trial.

After consulting the academic board, the treatment will be suspended for the following conditions: (1) serious adverse reactions (death or severe infections) that occur during the testing or (2) a guardian request withdraw their infant from the study at any time and without any consequences. The primary outcome and other data collected for participants until the date of withdrawal will be used and analyzed as part of the ITT population.

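### Growth at five follow-up visits is tested visit by visit in attenders only, so earlier measurements of children later lost do not inform the 104-week comparison; a repeated-measures model would be a cheap, modest improvement

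*Protocol article*

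**What the plan says.** Under Long-term outcomes after hospital discharge, the protocol article lists "Weight, length, and head circumference at 40 weeks postmenstrual age and 12, 26, 52, and 104 weeks corrected age". Table 1, under Clinical data collection, schedules the same visits.

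Under Statistical analysis, the whole provision for continuous outcomes is: "Continuous data will be analyzed using Student’s *t* test or the Mann-Whitney test as appropriate". The one regression model named there is for another kind of endpoint: "The effect of HC on the dichotomous outcomes will be assessed by multivariable logistic regression analysis". It does not reach growth.

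On children not seen, Clinical data collection says that "the missing data will be ignored in the analysis". Ethical and academic management adds that the primary outcome and "other data collected for participants until the date of withdrawal will be used and analyzed as part of the ITT population".

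The allowance for loss is in Sample size calculation: 81 per group, "which will be increased by 20% to compensate for potential dropouts during the follow-up, leading to 98 subjects per group". It is not tied to a particular visit.

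**The concern.** The same child is measured up to five times, and neither named test can combine visits. With missing values ignored, the plan yields 3 measures × 5 visits = 15 separate comparisons, each in that visit's attenders. What a lost child's earlier size says about its likely size at 104 weeks is left unused.

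Two things are at stake. The first is precision at the last visit, where cumulative loss is greatest. The second is protection against selective loss: if children who stop attending differ in earlier growth, and differ in different ways in the two arms, attenders are no longer a fair comparison and the named tests cannot correct for it.

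This matters because the trial's aim covers safety as well as efficacy, and the abstract names short- and long-term effects on growth among the secondary outcomes. Whether an early growth difference persists or is made up is an arm-by-visit question, and separate tests do not address it directly.

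**Working it through.** **Plan's own figure.** The article gives no standard deviation, effect size or sample size for growth, so there is none to reproduce. The loss allowance can be reproduced: 81 × 1.2 = 97.2, rounded up to 98. Falling from 98 to 81 is a loss of 1 − 81/98 = 17.3%. I use d = 17.3% and d = 20%, the second being the article's percentage read as a loss rate.

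**Precision, simple case.** Assume every child is seen at one earlier visit, a share d is missing at 104 weeks, and the two values correlate at ρ. Per arm of n children with variance σ²:

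- attenders only: (σ²/n) × 1/(1 − d)
- likelihood estimate using the earlier visit: (σ²/n) × [(1 − ρ²)/(1 − d) + ρ²]
- ratio: 1 − dρ²

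The reduction in standard error is 1 − √(1 − dρ²). Effective n per arm is 98(1 − d)/(1 − dρ²).

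| d | ρ | Variance ratio | SE reduction | Effective n per arm |
|---|---|---|---|---|
| 17.3% | 0.5 | 0.957 | 2.2% | 81.0 → 84.7 |
| 17.3% | 0.7 | 0.915 | 4.3% | 81.0 → 88.5 |
| 17.3% | 0.9 | 0.859 | 7.3% | 81.0 → 94.2 |
| 20% | 0.5 | 0.950 | 2.5% | 78.4 → 82.5 |
| 20% | 0.7 | 0.902 | 5.0% | 78.4 → 86.9 |
| 20% | 0.9 | 0.838 | 8.5% | 78.4 → 93.6 |

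**Precision, five visits with gradual loss.** Now spread the loss evenly, so that equal fifths of the lost children were seen at 0, 1, 2, 3 or 4 visits before leaving for good. Summing the information matrices over these patterns gives the variance of the 104-week mean.

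| Correlation between visits | SE reduction, d = 17.3% | SE reduction, d = 20% |
|---|---|---|
| Autoregressive 0.6 | 1.1% | 1.3% |
| Autoregressive 0.8 | 2.8% | 3.3% |
| Autoregressive 0.9 | 4.6% | 5.3% |
| Exchangeable 0.5 | 2.5% | 2.9% |
| Exchangeable 0.7 | 4.3% | 5.0% |

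Across both tables the gain runs from about 1% to about 9% of the standard error.

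**Scale.** At 80% power, taking α = 0.05 as two-sided (the article does not state sidedness), the detectable difference is (1.96 + 0.84) × √(2/n) SD. That is 0.40 SD with all 98 per arm, 0.44 with 81 and 0.45 with 78.4. The model recovers part of that gap.

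**Bias, illustrative case.** Suppose that in one arm only, 20% are lost and the log odds of loss change by 0.5 or 1.0 per SD of size at 52 weeks. The mean 52-week value of the remaining children then shifts by 0.096 or 0.173 SD. The 104-week mean shifts by ρ times that:

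- smallest: 0.7 × 0.096 = 0.067 SD
- largest: 0.9 × 0.173 = 0.156 SD

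Attenders-only tests carry this shift in full. A likelihood-based repeated-measures model removes it, because the value driving the loss is in the model. The largest shift is about a third of the 0.44–0.45 SD detectable difference (0.156/0.45 = 0.35).

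**The case against.** **Nothing is thrown away.** A reader might infer that early measurements of lost children are discarded. The article does not support that: they count at their own visits, and data up to withdrawal are kept in the intention-to-treat population. This stands. The defect is only that they do not inform later visits.

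**The gain is small.** Figures of 5–8.5% of the standard error (10–16% of the variance) arise only if all loss falls after 52 weeks, 20% are lost and the correlation is 0.7–0.9. With loss spread over visits or lower correlations, it can be near 1%. This stands, and the wider range is used here.

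**The bias is a constructed case.** A reader might infer that the planned comparison is biased. Nothing in the article shows that loss will depend on size differently by arm, and the trial is described as double-blind. If the dependence were the same in both arms, the shifts would largely cancel in the difference. This stands. The 0.07–0.16 SD shows what the named tests could not correct, not what is expected.

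**The model has limits.** It still gives 15 visit contrasts, so it is no remedy for multiplicity. It handles only loss explained by recorded values. If deaths before 104 weeks were treated as missing data, it would implicitly extrapolate growth beyond death. These points shape the fix.

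**This is analysis-plan detail.** Covariance structure and covariates commonly are, and the article does not rank the visits. But it goes further than silence: it names the tests and says missing values are ignored. An analysis plan that followed it would inherit the weakness.

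**Conclusion.** The point holds as a minor improvement. The stated methods and missing-data rule together make the 104-week growth comparison an attenders-only test that takes nothing from earlier visits. Visit-wise tests remain usable comparisons, so this is a less efficient and less protected choice rather than an invalid one.

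With 17–20% loss, a repeated-measures model would reduce the standard error at 104 weeks by roughly 1–9%. That range rests on assumed within-child correlations and timing of loss, neither of which the article gives. The model would also remove bias from loss that depends on recorded earlier growth and differs between arms. Whether such loss will occur is unknown.

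**What to change.** Amend the continuous-data sentence under Statistical analysis and the missing-data sentence under Clinical data collection for the growth outcomes, as follows:

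- For each of weight, length and head circumference, fit one mixed model for repeated measures over all five visits. Include arm, visit, arm-by-visit, center, gestational-age stratum, sex and actual age at visit, with an unstructured within-child covariance.
- Report the arm difference with its 95% confidence interval at each visit, prespecify 104 weeks as the main contrast, and give one arm-by-visit test for persistence or catch-up.
- State that the model assumes data are missing at random among surviving children.
- Report deaths separately, and do not treat growth after death as missing data.

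The cost is revised wording and slightly more programming; every measurement is already scheduled. The price in assumptions is reliance on missing at random, which is weaker than what the attenders-only tests need.

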### Outcomes

#### Primary outcome

The primary outcome is survival without moderate or severe BPD at PMA 36 weeks, which is defined as the following criteria: no respiratory support, spontaneous breathing FiO_2_ 0.21 for SpO_2_ 92%.

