#### Secondary outcomes

Amplitude-integrated electroencephalography (aEEG). A series of aEEGs will be monitored once a week for all preterm infants after 30 weeks PMA. Sleep-wake cycles of aEEG can be classified as absent, mature, or immature according to Hellstrom-Westas [31]. The PMA of mature sleep-wake cycles occurred will be used as one of the neurodevelopmental outcomes and be compared between two groups.Intraventricular hemorrhage (IVH) > grade II and/or periventricular leucomalacia (PVL). A series of cranial ultrasound scans will be performed regularly for all preterm infants, and these results will be extracted from the medical records after enrollment. IVH > grade II and/or PVL will be used as an adverse outcome to be compared between the groups [32].Brain volume at 40 weeks PMA. Total brain volume will be detected by using the functional MRI of the brain Software Library for automatic segmentation of the T1/T2 weighted images. The mean/median total brain volumes will be compared between groups at 40 weeks.Nosocomial infection, including cultured proven sepsis, meningitis, and pneumonia. Culture-proven infection is defined as a positive culture obtained from sputum, urine, blood, or cerebrospinal fluid of infants with clinical signs of infection, and pneumonia will be confirmed by abnormal lung examination (such X-ray, CT).Neonatal necrotizing enterocolitis (NEC). Bell stage II or more and/or focal intestinal perforation diagnosed by X-ray after enrollment to hospital discharge [33].Gastrointestinal bleeding diagnosed by the contents of the digestive tract.Retinopathy of prematurity (ROP). A series of fundus examinations will be arranged after enrollment, and ROP that needs treatment in any stage will be used as an adverse outcome [34].Anthropometric indices. Body length, head circumference, and body weight at 36 weeks of PMA.Hyperglycemia. Hyperglycemia that needs to be treated with insulin (serum glucose levels ≥ 200 mg/dl) after enrollment.Hospitalization days.

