## Discussion

In babies < 26^+0^ weeks gestational age, several problems, such as PDA, severe apnea, and high thorax compliance, may lead to noninvasive respiratory dependency at day 28 without any link to BPD. Furthermore, a higher rate of sepsis was observed in infants born at 24–25 weeks gestational age who were treated with hydrocortisone in a previous study [21]. Therefore, we will restrict the eligible patients to those between 26^+0^ and 30^+6^ weeks gestational age.

Because inflammation plays a key role in BPD, postnatal glucocorticoids are thought to be the most effective therapeutic strategy for preterm infants with a high risk for developing BPD [35], but they are accompanied by severe long-term adverse neurodevelopmental outcomes [11, 12]. These adverse outcomes seem to be associated with the timing of steroid exposure and the cumulative dosage of glucocorticoids; the earlier the treatment initiation and/or the larger the dosage, the higher the risk of adverse outcomes [11, 15].

Following the actual recommendations, many infants presenting with early BPD do not receive any anti-inflammatory therapy, and a high percentage of premature infants are still oxygen-dependent or on respiratory support at 36 weeks PMA (moderate or severe BPD) [27–29], which is associated with poor long-term pulmonary outcomes, including home oxygen therapy and a high rate of bronchopulmonary infections and rehospitalization [2]. A recent study showed that moderate or severe BPD at 36 weeks PMA was associated with increased mortality in the first year of life and moderate to severe neurodevelopmental impairment (55%) [6]. Thus, we hypothesize that anti-inflammatory treatment of infants meeting the NICHD criteria for BPD at 28 days of life may decrease the incidence of moderate or severe BPD at 36 weeks PMA and reduce long-term adverse outcomes.

In previous studies, early low-dose HC therapy in ventilator-dependent infants improved the rate of survival without BPD at 36 weeks PMA [21] without adverse neurodevelopmental outcomes at 2 years of age [22, 24]. Thus, it seems reasonable to use low-dose HC to treat infants with early BPD to improve pulmonary outcome. Accordingly, the efficacy and safety of this treatment must be proven by a randomized controlled trial.

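### The only stand-alone mortality outcome is limited to deaths related to premature birth, so some deaths after 36 weeks PMA may enter no listed comparison as deaths

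*Protocol article*

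**What the plan says.** Under Long-term outcomes after hospital discharge, the protocol article lists "Premature birth-related mortality from enrollment to 104 weeks corrected age". Table 1, under Clinical data collection, carries the same restriction in the row "Behavioral problems, premature birth-related mortality", marked only at 104 weeks corrected age. No other outcome is mortality on its own.

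Death also enters through the primary outcome: "The primary outcome is survival without moderate or severe BPD at PMA 36 weeks". Survival there is not limited by cause, but the assessment stops at 36 weeks PMA and is combined with BPD status.

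Three other statements bear on the point:

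- Infection is a secondary outcome as an event: "Nosocomial infection, including cultured proven sepsis, meningitis, and pneumonia".
- Adverse effects go to the independent academic board up to discharge: "Until the included patients are discharged, each potential adverse effect will be monitored and reported to the academic board within 48 h".
- Among the conditions for suspending treatment, Ethical and academic management names "serious adverse reactions (death or severe infections) that occur during the testing".

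**The concern.** Aim of the study covers both efficacy and safety. For safety, death from any cause needs no judgment. Death related to premature birth does: someone must decide for each death whether prematurity was responsible.

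The deaths of most safety interest are those that the drug might have caused, and these may be the ones whose link to prematurity is open to dispute. The protocol treats death and severe infection as possible serious adverse reactions. Its Discussion also cites an earlier hydrocortisone study in which "a higher rate of sepsis was observed" in infants of 24–25 weeks gestational age. That group is not eligible here, but the citation shows that infection is a recognised route of harm. If a late infection death is judged unrelated to prematurity, the listed mortality outcome does not count it.

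**Working it through.** The plan states no figure for mortality, so there is none to reproduce. The check has three parts: where a death can be counted, how much of follow-up is affected, and what one death is worth.

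**1. Where a death can be counted**

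| Listed item | Counts deaths of any cause? | Period | Compared between groups as death? |
|---|---|---|---|
| Primary outcome | Yes | To 36 weeks PMA | Only merged with BPD |
| Long-term mortality | No, only if related to premature birth | To 104 weeks corrected age | Yes, for the deaths counted |
| Nosocomial infection | No, counts the infection | After enrollment | No |
| Reports to the academic board | Adverse effects | To discharge | No comparison stated |

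A death after 36 weeks PMA that is judged unrelated to premature birth appears in no row as a death compared between groups. Clinical data collection adds that missing data will be ignored, so the same infant would also drop out of the Bayley, growth and behavior comparisons without being recorded there as a death.

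**2. Share of follow-up affected**

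Inputs: gestational age 26+0 to 30+6 weeks (Participants), randomization at day 28 (Randomization), follow-up to 104 weeks corrected from 40 weeks (Study design). Day 28 is taken as 4 weeks after birth and 36 weeks PMA as 36+0.

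- PMA at randomization: 26+0 + 4 weeks = 30+0, up to 30+6 + 4 weeks = 34+6.
- Time from randomization to the primary outcome: 36+0 − 30+0 = 6 weeks, down to 36+0 − 34+6 = 8 days.
- End of follow-up: 40 + 104 = 144 weeks PMA.
- Length of the mortality window: 144 − 30 = 114 weeks, down to 144 − 34+6 = about 109 weeks.
- Part after 36 weeks PMA: 144 − 36 = 108 weeks, which is 108/114 = 95% to 108/109 = 99% of the window.

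This is a share of time, not of deaths.

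**3. Size per death**

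Input: 98 per group (Sample size calculation). One death left out of one group moves the risk difference by 1/98 = 1.02 percentage points.

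For illustration, assume control mortality of 2% or 5% and a hydrocortisone excess of 3 or 5 points. None of these rates is in the documents. Expected deaths are 98 × rate. The counted risk ratio is (control + excess × share of the excess still counted) / control.

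| Control, excess | All deaths, control v HC | Risk ratio, all deaths | Half the excess classed out | All of it classed out |
|---|---|---|---|---|
| 2%, 3 points | 2.0 v 4.9 | 2.5 | 1.75 | 1.0 |
| 2%, 5 points | 2.0 v 6.9 | 3.5 | 2.25 | 1.0 |
| 5%, 3 points | 4.9 v 7.8 | 1.6 | 1.3 | 1.0 |
| 5%, 5 points | 4.9 v 9.8 | 2.0 | 1.5 | 1.0 |

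Power of a two-sided 5% comparison of all deaths (normal approximation for two proportions, 98 per group) is 21%, 39%, 13% and 26% in the four rows. Mortality will therefore be read from a few events, and the classification of two or three of them can change the picture. The table places every reclassified death in the hydrocortisone group, which is the extreme case.

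**The case against.** The strongest reply has four parts.

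- **Early deaths are already counted.** Any death up to 36 weeks PMA is a failure in the primary outcome, and the 10-day course ends before or only just after 36+0 even in the most mature infants. Nearly all deaths during treatment therefore reach a between-group comparison whatever their cause. This stands and confines the gap mainly to deaths after 36 weeks PMA. Within the primary outcome, however, deaths cannot be seen apart from BPD.
- **Assessors are blinded.** Cause would ordinarily be assigned without knowledge of group. This limits differential attribution. It does not help if the drug shifts the mix of causes: blinded assessors who class infection deaths as unrelated would remove more deaths from the group with more infections.
- **There is independent oversight.** The academic board receives adverse effects within 48 hours until discharge and reviews all data every 3 months. That protects participants, but it is not a stated comparison, and the reporting of adverse effects ends at discharge.
- **This is a condensed article.** Criteria for cause of death may well be in the full protocol or SAP, so their absence is not held against the plan. The restriction to one class of cause is different: the article states it twice.

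A reader might infer more than the text supports. The protocol does not say that infection or drug-related deaths are excluded; in this population a sepsis death could readily be classed as related to prematurity. It does not call death or severe infection expected effects of hydrocortisone; it names them as grounds for suspending treatment. Nor do the two outcomes contradict each other because one death can count in the first and not in the second: they have different definitions and windows.

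**Conclusion.** The point holds in a limited form. The plan fixes a cause-restricted mortality outcome and lists no all-cause alternative, so a death after 36 weeks PMA that is judged unrelated to premature birth is not compared between groups as a death. Each such death is worth about 1.0 percentage point of risk difference, assuming 98 infants per group in the denominator. How many there would be cannot be derived from the documents; the risk ratios shown rest on assumed rates and on a one-sided reclassification. Exclusion is possible, not certain. The primary analysis is unaffected. This is a weakness in safety reporting that should be corrected.

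**What to change.** In Long-term outcomes after hospital discharge and in Table 1, define the outcome as all-cause mortality from randomization to 104 weeks corrected age. Report causes of death descriptively by group, assigned blind to treatment, with deaths related to premature birth at most as a breakdown of the total.

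The cost is a wording change in two places, submitted to the ethics committee as the protocol requires for any amendment. The sample size does not change and no visit is added. The article does not say that vital status is recorded at each contact, but the contacts already planned at 40 weeks PMA and at 12, 26, 52 and 104 weeks corrected age can supply it.
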